#### Exploratory Hypotheses

Correlation will be good between baseline investigator assessment of participant information and involvement preference and participant report of DA acceptability. Correlation will be good between high baseline participant information and involvement preference and high acceptability of DA to participants. Correlation will be good between baseline investigator assessment of distress and participant report of distress. Participants will be willing to complete the EuroQol 5-Dimensions (EQ-5D-5L) questionnaire, a health utility measure.

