### Study Design

#### Screening

Potentially eligible patients are identified during the planning of their initial treatment strategy at participating Australian sites during multidisciplinary meetings and at surgical and medical oncology appointments. Patients are approached by their clinician during their appointment to consider receiving additional information about the DOMINO study via a Web link that is sent to the patient via an auto-generated email. At the time of the initial offer of study participation, patients are asked to indicate written consent on a screening form for their personal information (name, email address, and telephone number) to be provided to the ANZBCTG. A Web link to the study consent page and questionnaires is then sent to them by email. Patients who consent to share personal information are provided with a copy of their signed screening consent form along with study-specific written information about their breast cancer. This information is intended to aid understanding of their diagnosis when using the decision aid. Clinicians are required at this time to record details regarding the primary reason for NAST, as well as an opinion of the patient’s current distress levels and information preferences. The completed screening consent form is sent via Teleform (Hewlett Packard) fax to the ANZBCTG to be verified, and email contact with the patient is established.

If the patient does not consent to share personal information, the clinician records information on the screening consent form so a log can be kept of each patient who is ineligible and screened out, eligible but not offered participation, and offered participation but declines. The number of patients who consent to screening but do not participate in the study will also be recorded. Screening data will be used to describe feasibility of DA use.

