#### Registration

Patients are registered to the study through the following process. The screening form is received at the ANZBCTG for validation and confirmation of eligibility criteria. Patients who consent to release their details on the screening form receive an automatically generated email. These patients are now considered eligible for the DOMINO study. Patients who access, read the online DOMINO Information Statement and Consent page, and agree to participate in the study are redirected to a series of demographic questions. On submission of responses to demographics and consent, patients are considered registered to the study. Patients at this stage are also given the opportunity to opt in to a telephone interview. Eligible patients have a 6-week window in which to view and agree to participate in the DOMINO study before being considered a screen failure. We aim to register 50 patients to the DOMINO study.

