#### Electronic Communication Processes

At the point of registration, patients are requested to enter a password to access the DOMINO website. Thereafter, an individual’s username is defined by their email address.

Site trial coordinators input dates of patient appointments and projected treatment completion dates, which are then used to calculate and trigger all communication with the patient and reminders to site coordinators. Pre-designed patient and site coordinator emails are sent automatically at specific timepoints, as guided by information entered by sites as to the treatment decision (either NAST or surgery), to patients. A reminder email is sent to the patient if the survey remains unsubmitted 3 calendar days after the initial email. If after an additional 2 calendar days a patient has not submitted a questionnaire, an automatically generated email is sent to the ANZBCTG study coordinator prompting a telephone call to the patient. Site study coordination staff are sent automatically generated emails prompting completion of data via the online system or informing them of their patient’s submission of a questionnaire.

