#### Questionnaire Administration

A series of validated questionnaires where available, and custom designed where a questionnaire is not available, are presented to patients at four timepoints before and after access to the decision aid (see Table 1). Prior to access to the decision aid, patients are asked to report demographics and to complete 6 questionnaires that address decisional conflict, decision-making preference, information and involvement preferences, anxiety, distress, and an optional health economic instrument.

At the completion and submission of the first set of questionnaires, patients are able to access an electronic copy of the decision aid. This document can be printed, saved, and accessed by a patient at any stage of the study by logging in to the DOMINO website. Patients are asked to complete and read the decision aid prior to attending their next appointment with their clinician, at which time a decision regarding treatment may be made. At this visit, the clinician refers to the decision aid and asks whether the patient has any questions about it. After the attendance at an appointment where a decision was made regarding treatment and specific data have been entered by the site, the patient receives an autogenerated email informing them that a second set of questionnaires is available for completion. Questionnaires at this timepoint ask the patient to reflect on the information provided in the DA and its role in their treatment decision. Patients who do not submit both questionnaire sets 1 and 2 will be replaced to ensure that pre-post outcomes are recorded for 50 patients.

Based on treatment details supplied by the site trial coordinator about treatment option chosen and date of completion, an email link to questionnaire set 3 is sent to the patient. This questionnaire is to be completed after the initial treatment strategy of either chemotherapy or surgery. It is expected that most participants will then proceed with surgery or systemic therapy respectively as their subsequent treatment strategy. This assessment aims to determine the effect of the first treatment strategy on decision-related outcomes, without the influence of the alternative strategy.

Questionnaire set 4 is answered 12 months after registration, to investigate longer-term outcomes including anxiety, distress, regret, and recollection of pathology results. This is the last questionnaire, and participants complete their study involvement at this time.

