**Decision-making preference questionnaire**						
	Preferred	X	X			
	Actual		X			
Distress thermometer		X	X	X	X	X
Information and involvement preferences		X	X			
EQ-5D-5L (optional)		X	X	X	X	X
Knowledge of decision aid information			X			
Decision aid feedback			X			
Satisfaction with decision scale			X			
Fear of progression (FOP 12)			X	X	X	
Decision regret scale				X	X	X
Fear of Cancer Recurrence Inventory				X	X	X
Participant-reported pathology results (NAST only)						X

^a^Postchemotherapy, before surgery.

^b^Postsurgery, before adjuvant chemotherapy.

^c^12 months (+/- 1 month) after registration.

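### Clinician-rated and patient-reported distress are compared only by correlation, which cannot show systematic under- or over-rating; an agreement measure and the interval between ratings should be added

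*Protocol article*

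**What the plan says.** The hypothesis stands in the protocol article under Exploratory Hypotheses: "Correlation will be good between baseline investigator assessment of distress and participant report of distress". No coefficient, no cut-off for a good value and no timepoint for the participant's report are given there, and Statistical Analysis describes no method for this comparison.

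The two ratings come from different study steps:

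- **Clinician.** Under Screening, at the initial offer of participation, the clinician records the main reason for NAST "as well as an opinion of the patient’s current distress levels and information preferences". The scale is not stated.
- **Patient.** Under Registration, "Eligible patients have a 6-week window in which to view and agree to participate in the DOMINO study before being considered a screen failure". Questionnaire set 1 follows registration and precedes access to the decision aid (Questionnaire Administration). Table 1 lists the "Distress thermometer" at that assessment and at every later one.

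For another paired comparison, preferred against achieved decisional control, the article hypothesises high agreement (Secondary Hypotheses and Outcome Measures) and plans a weighted kappa with a McNemar test (Statistical Analysis).

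**The concern.** The other two correlations under Exploratory Hypotheses relate different constructs: information and involvement preference on one side, acceptability of the decision aid on the other. Correlation is the natural measure there. The distress comparison is different, because two raters report on one quantity in one patient. A reader will want to know whether the clinician's opinion is close to the patient's own report and, if not, in which direction it errs. Correlation answers only whether the two rank patients similarly along a line.

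Two separate limits follow:

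- A good correlation is compatible with clinicians under- or over-rating distress throughout.
- A poor correlation may reflect a real change in distress between the two ratings, not misjudgement by the clinician.

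What is at stake is how far this one exploratory comparison can be interpreted.

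**Working it through.** **Plan's own figure.** The article states no coefficient, threshold, power or precision for this comparison, so there is nothing to reproduce. The only input below taken from the document is the planned sample of 50. The common 0-10 scale, equal SDs, r, shift and stability are assumptions.

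**1. Effect of a constant shift.** Adding a constant to one rater's scores leaves r unchanged. With equal SDs, Lin's concordance coefficient is

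CCC = 2·r·SD² / (2·SD² + shift²).

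With r = 0.70 and SD = 2.5, the numerator is 2 × 0.70 × 6.25 = 8.75:

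| Under-rating (points) | r | CCC |
|---|---|---|
| 0 | 0.70 | 8.75/12.5 = 0.70 |
| 1 | 0.70 | 8.75/13.5 = 0.65 |
| 2 | 0.70 | 8.75/16.5 = 0.53 |
| 3 | 0.70 | 8.75/21.5 = 0.41 |

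Over-rating by the same amount gives the same CCC, because the shift enters squared.

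**2. Range over the assumptions.** For a 2-point shift and SD from 2.0 to 3.0, CCC runs from 0.47 to 0.57 at r = 0.70 and from 0.53 to 0.65 at r = 0.80.

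**3. Rounding and the ends of the scale.** A simulation of 400,000 pairs, with scores rounded and clipped to 0-10 (patient mean 5, SD 2.5, underlying r 0.70), gives r 0.69 and CCC 0.69 with no shift. With a 2-point shift it gives r 0.68 and CCC 0.51. The correlation barely moves.

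**4. What an agreement analysis would show.** The SD of the differences is 2.5 × √(2 × 0.30) = 1.94. With 2 points of under-rating, the limits of agreement are −2 ± 1.96 × 1.94, or −5.8 to +1.8.

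**5. Precision with 50 pairs.** An observed r of 0.70 has a 95% CI of 0.52 to 0.82 (Fisher z, half-width 1.96/√47 on the z scale). The mean difference has a 95% CI of about ±1.96 × 1.94/√50 = ±0.54 points. A 2-point bias would be plain in the mean difference and invisible in r.

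**6. Effect of the time gap.** If distress changes between the ratings independently of clinician error, the observed r is about the same-time r multiplied by the stability of distress over the gap. From r = 0.70:

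- stability 0.9: 0.63
- stability 0.7: 0.49
- stability 0.5: 0.35

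Ordinary drift therefore works downward only.

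**The case against.** The strongest reply is that the protocol hypothesises a correlation and a correlation coefficient answers that hypothesis. A reader might infer that the study means to show, through a good correlation, that clinicians judge distress correctly. The article never says so, and it should not be faulted for a conclusion it does not draw. This stands.

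A reader might also infer that ratings up to six weeks apart could make a good correlation misleading. The documents do not support that. Ordinary drift lowers r, so the gap bears on a poor result. Six weeks is the limit for registration before a patient counts as a screen failure, not an expected interval. Set 1 must be submitted before the decision aid opens, and the aid is to be read before the next appointment. The Discussion puts the wait for a medical oncologist at several days or longer. The intended pathway therefore points to shorter gaps, although no maximum interval between the two ratings is stated.

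Two further points stand. The clinician's scale is not given, so the figures above are illustrations and nothing in the article shows that clinicians do under-rate. Pairing with the thermometer in set 1 is an inference, though the natural one.

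The last reply is that coefficient, cut-off and added analyses belong in a fuller document. That holds for the coefficient and the cut-off. It does not dispose of the point, because the article itself names correlation as the measure for two ratings of one construct, while choosing an agreement statistic for its other paired comparison.

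**Conclusion.** The point holds in a limited form. As worded, the hypothesis cannot reveal systematic under- or over-rating of distress, because r ignores a constant shift. That is a mathematical property and depends on none of the assumed values. The size does depend on them: with a common 0-10 scale and equal SDs of 2.0 to 3.0, a 2-point shift takes concordance from 0.70 to between 0.47 and 0.57, or from 0.80 to between 0.53 and 0.65, with r unchanged.

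The separate timing point is that a change in distress between screening and set 1 can lower r, so a poor correlation would be hard to read.

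The importance is low. The hypothesis is exploratory, and no primary or secondary conclusion rests on it.

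**What to change.** Keep the correlation and add an agreement analysis for this hypothesis:

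- If both ratings use the same numeric scale, report the mean clinician-minus-patient difference with its 95% CI and the limits of agreement. A concordance coefficient is optional.
- If the clinician item is categorical, report weighted kappa on matched categories, with the direction of disagreement.
- State that the patient's pre-decision-aid thermometer is the comparator, if that is intended.
- Describe the interval in days between the two ratings where dates are available. This also helps in reading the mean difference, since an average change in distress over the gap would appear there as clinician bias. A repeat in pairs taken within 7 days is optional and would use fewer pairs.

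The cost is a little more analysis and wording, with no new patients or questionnaires. Intervals will be wide at about 50 pairs.

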#### Knowledge Questionnaire

A custom-designed 7-item knowledge questionnaire has been developed based on the content of the DA to test recall and comprehension (see Multimedia Appendix 2). Questions were taken from information throughout the DA. The number of correct responses will be transformed to a score out of 100.

#### Demographic, Tumor, and Treatment Information

The following demographics will be recorded: age, marital status, level of education, health insurance, occupation, and native language. Tumor characteristics consist of tumor size, nodal status, estrogen/progesterone receptor, HER2 amplification, and grade. Investigations and treatment received include duration of chemotherapy, radiotherapy, surgical procedure(s) performed, biopsies, and imaging performed.

#### Telephone Interview

Participants will be asked to participate in a semistructured interview using a pre-planned interview guide, to gain a deeper understanding of their attitude toward the utility and acceptability of the DA. Participants are asked at the time of consent to tick a box indicating their willingness to be contacted for an interview. Interviews will undergo immediate initial analysis and will be conducted until thematic saturation is reached, defined as no new major themes in three consecutive interviews. Further rounds of analysis will be conducted in an iterative fashion after all interviews are complete. Interviews will be recorded, transcribed verbatim, and analyzed using qualitative methodology. Qualitative descriptive methodology will be used, as is appropriate when lived experience, views, and preferences are the target of investigation, and there are little existing data available. This method can be used to gain a rich description of an experience, founded in existing knowledge and interpreted in the context of the clinical experience of the research group [39].

#### Clinician Questionnaire

After 50 patients have completed their post-DA questionnaire, all clinicians will receive an electronic questionnaire. The questions include specialty (surgeon or medical oncologist), intent to use the DA in routine clinical practice, patient selection for DA use, effect on consultation duration and number, apparent effect on decision making, and comments on content. The DA will be considered acceptable to clinicians if more than 50% report that they would use the DA in routine clinical practice.

#### Questionnaire Administration

A series of validated questionnaires where available, and custom designed where a questionnaire is not available, are presented to patients at four timepoints before and after access to the decision aid (see Table 1). Prior to access to the decision aid, patients are asked to report demographics and to complete 6 questionnaires that address decisional conflict, decision-making preference, information and involvement preferences, anxiety, distress, and an optional health economic instrument.

At the completion and submission of the first set of questionnaires, patients are able to access an electronic copy of the decision aid. This document can be printed, saved, and accessed by a patient at any stage of the study by logging in to the DOMINO website. Patients are asked to complete and read the decision aid prior to attending their next appointment with their clinician, at which time a decision regarding treatment may be made. At this visit, the clinician refers to the decision aid and asks whether the patient has any questions about it. After the attendance at an appointment where a decision was made regarding treatment and specific data have been entered by the site, the patient receives an autogenerated email informing them that a second set of questionnaires is available for completion. Questionnaires at this timepoint ask the patient to reflect on the information provided in the DA and its role in their treatment decision. Patients who do not submit both questionnaire sets 1 and 2 will be replaced to ensure that pre-post outcomes are recorded for 50 patients.

Based on treatment details supplied by the site trial coordinator about treatment option chosen and date of completion, an email link to questionnaire set 3 is sent to the patient. This questionnaire is to be completed after the initial treatment strategy of either chemotherapy or surgery. It is expected that most participants will then proceed with surgery or systemic therapy respectively as their subsequent treatment strategy. This assessment aims to determine the effect of the first treatment strategy on decision-related outcomes, without the influence of the alternative strategy.

Questionnaire set 4 is answered 12 months after registration, to investigate longer-term outcomes including anxiety, distress, regret, and recollection of pathology results. This is the last questionnaire, and participants complete their study involvement at this time.

**Table 1 table1:** Questionnaire content according to assessment timepoint.

		Pre-DA assessment	Posttreatment decision assessment	Postchemo assessment (NAST)^a^	Postsurgery (non-NAST)^b^	Posttreatment assessment^c^
Decision conflict scale		X	X			
State-Trait Anxiety Inventory‒6 Anxiety		X	X	X	X	X
**Decision-making preference questionnaire**						
	Preferred	X	X			
	Actual		X			
Distress thermometer		X	X	X	X	X
Information and involvement preferences		X	X			
EQ-5D-5L (optional)		X	X	X	X	X
Knowledge of decision aid information			X			
Decision aid feedback			X			
Satisfaction with decision scale			X			
Fear of progression (FOP 12)			X	X	X	
Decision regret scale				X	X	X
Fear of Cancer Recurrence Inventory				X	X	X
Participant-reported pathology results (NAST only)						X

^a^Postchemotherapy, before surgery.

^b^Postsurgery, before adjuvant chemotherapy.

^c^12 months (+/- 1 month) after registration.

### Statistical Analysis

A sample size of 50 participants is planned. The primary analysis will include all registered patients and clinicians as two separate cohorts. The proportion of patients and investigators who consider the DA acceptable will be reported with 95% exact confidence limits. The primary outcome will be considered positive if more than half of patients and clinicians consider the DA acceptable, and feasible if more than half of eligible patients who are offered participation register and subsequently use the DA. Assuming a sample size of 50 participants, the primary outcome of percentage of participants finding the DA acceptable can be estimated to within ±15% based on 95% exact confidence limits. To ensure that the lower 95% one-tailed exact confidence limit is greater than 50%, at least 32 of the 50 participants will need to indicate DA acceptability. Although the study is not powered to test the secondary hypotheses, there is 80% power to detect a change of at least 0.40 standard deviations from the pre- to post-DA assessments using a two-tailed *t*-test with alpha=.05 and a sample size of 50 participants.

Changes in secondary outcome measures from the pre-DA assessment, including decisional conflict, information preference, anxiety, distress, and fear of progression, will be evaluated using repeated measures analysis of covariance (ANCOVA). All outcomes will be described using mean and standard deviation for continuous measures and frequency for categorical outcomes. If data are skewed, median and interquartile range will be reported and the appropriate linearizing transformation will be used. Analyses will be performed unadjusted and adjusted for age, level of education, information preferences, and tumor characteristics (size, grade, node involvement, ER/PR/HER2). Agreement in decisional control before and after using the DA, and between preferred and actual control, will be assessed using a weighted kappa statistic with McNemar test. Knowledge will be reported as mean proportion of items correct with standard deviation. Cost will be recorded using Australian Medical Benefits Scheme item numbers and Pharmaceutical Benefits Scheme prices, and a comparison made between those who receive surgery first and those who receive systemic therapy first.

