#### Secondary Hypotheses and Outcome Measures

We hypothesize that with use of the DA the Decisional Conflict Scale score will decrease [30]; knowledge about NAST, using a custom-designed questionnaire, will increase; information and involvement preference will increase [31]; agreement between preferred and achieved decision control will be high, based on an adaptation of the Control Preferences Scale to include achieved control [14]; and the Control Preferences Scale score will increase [14]. Further, there will be no change in cost of health care delivery or in the 6-item State-Trait Anxiety Inventory score [32]. Fear of cancer progression will be unchanged while receiving neoadjuvant therapy [33]; the Decisional Regret score after chemotherapy and after surgery will be low [34]; fear of cancer recurrence score will be low [35]; distress thermometer score will decrease [36, 37]; satisfaction with decision score will be high [38]; and there will be no change in outcomes between those who decided to receive neoadjuvant chemotherapy with those who decided not to have neoadjuvant therapy.

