## Discussion

### Principal Considerations

This study intends to evaluate the acceptability and feasibility of a DA for women with operable breast cancer who have been offered NAST. It is designed as a single arm pre-post study to allow all participants access to the intervention. The population of Australian women who currently receives NAST is relatively small, limiting the feasibility of a larger, randomized controlled trial with comparative outcomes. However, the proportion of patients receiving NAST in Australia and New Zealand is expected to increase as a result of increased awareness, availability of neoadjuvant clinical trials, and from the results of ongoing neoadjuvant and post-neoadjuvant trials.

The study primary endpoints are pragmatic. We expect that some participants will not find the DA beneficial, based on their decision-making style and information-seeking behavior. However, we hypothesize that the number who find it helpful in their decision-making process will be greater than the number who do not find it useful. Because DAs have variable use across centers and individual clinicians [40], feasibility was included as an endpoint. A screening log is designed to quantify the number of patients who are seen at recruiting sites who are candidates for NAST for operable breast cancer; are eligible for the study; are offered study participation; accept study participation; and go on to access the DA. This will identify the proportion of eligible patients who are not offered participation (clinician feasibility) and the proportion of eligible patients who do not access the DA after being offered it (patient feasibility). Acceptability will be assessed using direct questions to patients and clinicians.

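### The adjusted comparison of women who chose NAST with those who did not takes no account of pre-choice psychological state for regret, satisfaction and the two fear outcomes

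*Protocol article*

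**What the plan says.** All references are to the protocol article.

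- **Comparison.** Secondary Hypotheses and Outcome Measures states that "there will be no change in outcomes between those who decided to receive neoadjuvant chemotherapy with those who decided not to have neoadjuvant therapy". The outcomes are not named one by one.
- **Design.** Principal Considerations says: "It is designed as a single arm pre-post study to allow all participants access to the intervention". Which treatment comes first is therefore settled by patient and clinician.
- **Adjustment.** Statistical Analysis says: "Analyses will be performed unadjusted and adjusted for age, level of education, information preferences, and tumor characteristics (size, grade, node involvement, ER/PR/HER2". No other section adds a covariate.
- **Baseline use.** Statistical Analysis assigns repeated measures ANCOVA to "Changes in secondary outcome measures from the pre-DA assessment, including decisional conflict, information preference, anxiety, distress, and fear of progression".
- **What is collected before the aid.** Under Questionnaire Administration, patients first "complete 6 questionnaires that address decisional conflict, decision-making preference, information and involvement preferences, anxiety, distress, and an optional health economic instrument".
- **What is not.** In Table 1, the row "Satisfaction with decision scale" is marked only after the treatment decision. The fear of progression row is first marked there. The row "Decision regret scale" and the Fear of Cancer Recurrence Inventory are marked only from the post-chemotherapy or post-surgery assessment onward. None of the four has a pre-aid mark.

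**The concern.** In a comparison of self-chosen groups, a covariate matters when it precedes the choice and may be related both to the choice and to the outcome. Anxiety and distress just after diagnosis are natural candidates when the outcome is later regret, fear or satisfaction. For anxiety, distress and decisional conflict as outcomes, the change from the pre-aid assessment already brings in their own baseline. The other four outcomes have no baseline, so only the covariate list could account for prior psychological state, and it does not.

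A difference between the choice groups on those four scales could then partly reflect who was more distressed beforehand. Because the hypothesis is one of no difference, bias in the opposite direction could also hide a real difference and appear to confirm the hypothesis. Either result would be reported as adjusted.

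**Working it through.** **1. The plan's own figure.** The article gives no figure for this comparison. Its nearest figure is 80% power for a 0.40 SD pre-post change with n = 50 and two-tailed alpha 0.05. A paired t-test with noncentrality 0.40 × √50 = 2.83 and 49 df gives 79.2%; the normal approximation gives 80.7%. The figure reproduces but does not bear on the choice-group comparison. There, an unadjusted two-sample t-test on 50 women has 80% power only for differences of about 0.81 SD (25/25) to 1.35 SD (45/5).

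**2. Inputs.** From the article: n = 50, alpha 0.05 two-tailed, and the covariate list. Not in the article, so assumed:
- split 35/15, with 25/25 and 40/10 for range
- difference g in the pre-aid score between choice groups: 0.3 to 0.5 SD
- within-group correlation r of that score with the later outcome: 0.5 to 0.6
- no true group effect
- planned covariates unrelated to the pre-aid score
- coding of the planned covariates: age 1, education 2, information preferences 1, size 1, grade 2, node 1, ER, PR and HER2 3, total 11 terms

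**3. Spurious difference** = g × r.
- 0.3 × 0.5 = 0.15 SD
- 0.5 × 0.5 = 0.25 SD
- 0.5 × 0.6 = 0.30 SD

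**4. Standard error in the planned adjusted model.** Without covariates it is √(1/n₁ + 1/n₂); at 35/15 this is √(0.0286 + 0.0667) = 0.309. Eleven unrelated terms multiply it by √(47/(47 − 11)) = 1.14, giving 0.353. Residual df are 50 − 2 − 11 = 37.

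**5. False-positive rate.** This is the two-sided 5% rejection probability from a noncentral t with 37 df and noncentrality (spurious difference)/(standard error):

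| Split | SE, 11 terms | 0.15 SD | 0.25 SD | 0.30 SD |
|---|---|---|---|---|
| 25/25 | 0.323 | 7.4% | 11.7% | 14.8% |
| 35/15 | 0.353 | 7.0% | 10.6% | 13.2% |
| 40/10 | 0.404 | 6.5% | 9.3% | 11.2% |

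At 35/15 with no covariates (SE 0.309, 48 df), the 0.25 and 0.30 SD columns would be 12.5% and 15.9%. Those values describe the unadjusted analysis, not the adjusted model in question.

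**6. Effect of adding the score.** In simulation of the 11-term model at 35/15 with g = 0.5 and r = 0.5, adding the pre-aid score removes the assumed bias. The mean standard error falls from 0.350 to 0.315 with one score (0.035/0.350 = 10%) and to 0.329 with three (0.021/0.350 = 6%). The second and third scores therefore give back part of the gain.

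**The case against.** **The causal link is not documented.** A reader might infer that distress drives the choice of NAST and that the comparison is therefore biased. The documents do not support that. The Introduction says that distress makes it harder to engage women in this decision, not which option they then choose. The imbalance and the correlation are assumptions, and the direction of any bias is unknown. This stands, and it makes the size conditional.

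**The model for this comparison is not spelled out.** The hypothesis names no outcomes. Of the four scales, only fear of progression is in the ANCOVA list, and the only between-choice comparison that Statistical Analysis describes is cost. Details may sit in an analysis plan that is not shown. This stands in part. The covariate sentence is nevertheless general and explicit. If it does not apply here, the article states no adjustment for the comparison at all. The ANCOVA also cannot supply a baseline for fear of progression, because Table 1 shows none.

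**Tumor features are the better-supported confounders.** A reader might infer that the tumor terms are wasted and could be condensed to the subtype grouping in the aid. That does not hold. The grouping is hormone-receptor and HER2 status only, so size, grade and nodes would be dropped. The Introduction gives down-staging of larger tumors and of the axilla as reasons for NAST.

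**The list is not wholly free of patient-reported measures.** Information preferences are in it. That is correct, but they do not measure anxiety or distress.

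**Little rests on it.** The comparison is secondary, and the article says that the study is not powered for its secondary hypotheses. This stands and limits the priority, but low power does not make a biased adjusted estimate acceptable when a remedy is already in the data.

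**Conclusion.** The point holds in a limited form. The stated covariate list leaves out every pre-aid anxiety, distress and decisional-conflict score. For regret, satisfaction, fear of progression and fear of recurrence, no baseline of the outcome fills the gap. The adjusted NAST versus non-NAST comparison of these four therefore takes no account of psychological state before the choice.

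Whether this produces bias in this study cannot be known from the documents. If the pre-aid score differs by 0.3 to 0.5 SD between choice groups and correlates 0.5 to 0.6 with the outcome, the spurious difference is 0.15 to 0.30 SD. The false-positive rate is then about 7% to 13% at 35/15 with the 11 planned terms. Acceptability and feasibility, the primary endpoints, are untouched. This is a worthwhile, nearly free improvement to a secondary analysis, not a flaw that threatens the study.

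**What to change.** Before analysis, specify for the NAST versus non-NAST comparison:

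1. For the four outcomes without a pre-aid value, add one pre-aid psychological score from questionnaire set 1 to the adjusted model: STAI-6 or the distress thermometer, chosen in advance. Add decisional conflict as well only if the model supports it.
2. For anxiety, distress and decisional conflict, use the outcome's own pre-aid score.
3. Keep tumor size, grade, node involvement and ER/PR/HER2.
4. Label the comparison observational wherever it is reported.

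**Cost.** Analysis wording only, since the scores are already collected. The model gains one to three terms in 50 women: under the assumed coding, 12 to 14 covariate terms instead of 11, and residual df of 36 to 34 instead of 37.

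**Limit.** Adjustment does not make set 3 comparable, because it follows chemotherapy in one group and surgery in the other. The report should say so.
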